### Participant Timeline

The estimated study duration is 6 months from the first to last patient recruitment. Each patient will remain in the study until discharge or death.

### Sample Size

The sample size has been determined to be 120, with 30 patients in each group (AS19, PAU19, POL19, and ARD19). In addition, a control group of 30 healthy individuals (negative for SARS-CoV-2) is required. From our experience, we presume that with this sample size, we would be able to identify a transparent variation in immune cell counts and serum cytokine levels. This conforms to most of the immunologic studies in the literature. Moreover, with this sampling, we can identify significant differences in the order of 20% to 30% in terms of the phenotype and function of immune cells.

### Data Collection and Management

Data will be collected using the following 3 approaches: (1) an experimental analysis for clusters of patients to study the innate immune response and to identify genetic profiles; (2) an epidemiological analysis to identify patient vaccination history; and (3) a clinical analysis to detect the immunological profile.

### Sample Description and Collection for the Experimental Analysis

For the specific analysis, to study the innate immune response and to identify the genetic profiles, we will analyze NK cells, monocytes, and CD4^+^ and CD8^+^ T cells from peripheral blood in both the healthy group (tested negative for SARS-CoV-2) and sick subgroups (AS19, PAU19, POL19, and ARD19). For each patient, a venous blood sample will be obtained (15 mL in EDTA solution).

### Preparation of Plasma and Isolation of PBMCs From Blood

From different groups of patients, blood samples (10-15 mL) will be drawn in EDTA tubes and centrifuged at 360 *g* for 10 minutes to obtain plasma that will be stored at −80°C for subsequent analysis of cytokines and chemokines of interest by enzyme-linked immunosorbent assay (ELISA) (IL-1β, IL-6, TNFα, IFNα, IL-10, IL-12, CCL2, and CXCL10) at the end of enrollment.

The cell pellets will be brought back to the initial volume with phosphate-buffered saline (PBS) (Euroclone) and diluted 1:1 (v/v) with PBS. It will then be subjected to density gradient stratification with Lymphosep (Biowest) at 500 *g* for 30 minutes at room temperature with no brake. The PBMCs derived from the white ring will be collected, washed twice in PBS, and then used for subsequent experiments using a flow cytometer assay [25]. The in vitro culture using PBMCs can vary from ex vivo 1 day to a few days, and cells will be maintained in RPMI 1640 medium (Euroclone), supplemented with 10% fetal bovine serum (FBS) (Euroclone), 2 mM l-glutamine, and 100 U/mL penicillin and 100 μg/mL streptomycin (both Euroclone), at 37°C and 5% CO_2_.

To perform ex vivo flow cytometry cell phenotype analysis, 2.5×10^5^ fresh or frozen total PBMCs per tube will be stained for 30 minutes at 4°C with monoclonal antibodies (mAbs) (Becton Dickinson [BD]) as follows: CD3-BB700, CD56-APC, CD16-PE-Cy7, CD159a (NKG2A)-BV510, NKG2C-PE, NKGD2-PE, DNAM-1-PE, CD25-PerCP-Cy5.5, CD69-PE, CD279 (PD1)-BUV737, TIGIT-BV786, CD96-BB515, and CD366 (TIM3)-BV421. Samples will be acquired using BD LSR Fortessa. Following the forward/side scatter setting, NK cells will be divided into 2 cell subsets (ie, CD3^−^ and CD56^dim^ CD16^+^ cells [CD56^dim^ NK cells, the major subset, about 90%] and CD3^−^ and CD56^bright^ CD16^−/low^ cells [CD56^bright^ NK cells, the minor subset, about 10%]). Other marker expressions will be evaluated in both subsets of gated cells.

For ex vivo flow cytometry cell evaluation of monocyte phenotypes, 2.5×10^5^ fresh or frozen total PBMCs per tube will be stained for 30 minutes at 4°C with mAbs (BD) as follows: CD45-APC, CD14-FITC, CD16-PE-Cy7, PE-CD209, and PE-CD80. Following the forward/side scatter setting, monocytes will be divided into 3 subsets (ie, CD14^++^ and CD16^−^ cells [the classical subset, about 90%], CD14^++^ and CD16^+^ cells [the intermediate subset, about 10%], and CD14^−/low^ and CD16^++^ cells [the nonclassical subset]) [33].

We will also evaluate phenotypes for CD4^+^ and CD8^+^ T cells and the CD4/CD8 T ratio using 2×10^5^ fresh or frozen total PBMCs, as previously described, with the following mAbs (BD): CD3-PerCP, CD4-APC, CD8-V450, and CD25-PE. We will also assess T regulatory (Treg) cells with CD3-PerCP, CD4-APC, and CD25-PE. Furthermore, we will analyze T-cell responses toward the spike protein using 15-mer peptides (6 nM each, final concentration; 11 amino acids overlapping) of the full-length spike protein (Milteny Biotec). The IFNγ response by spike-specific T cells will be studied by intracellular staining with a fluorescence-activated cell sorter. We will perform cytofluorimetric intracellular staining by using a Cytofix/Cytoperm fixation and permeabilization kit, according to the manufacturer’s protocol (BD). Briefly, 5×10^5^ PBMCs will be first stained with surface mAbs, such as CD3, CD4, and CD8, for 30 minutes at 4°C. Then, cells will be washed and treated with 200 μL of cytofix/cytoperm solution for 30 minutes at 4°C. Then, cells will be washed and incubated with anti-IFNγ mAbs (BD) for an additional 30 minutes. After a further washing step, cells will be analyzed using flow cytofluorimetric assay.

PBMCs will also be stimulated in vitro for 6 h with different types of stimuli, such as lipopolysaccharide (LPS) (Sigma Aldrich) (recognized by TLR4), poly (I:C) (Sigma Aldrich) (recognized by TLR3), poly (I:C) plus IL-2 plus IL-12, and phorbol myristate acetate (Sigma Aldrich) plus ionomycin (Sigma Aldrich) in the presence of monensin (Golgi Stop, BD) and brefeldin A (Golgi Plug, BD). This procedure will allow the detection of cytokine/chemokine production from NK cells, monocytes, and T cells by using a flow cytometry intracellular assay, as described previously [34]. For NK cells, we will measure IFNγ-BV650, TNFα-PE, CCL2-PE, and CXCL10-PE by intracellular staining and CD107a-PE (surface degranulation marker) using flow cytofluorimetric assay (BD). For monocytes, we will investigate IL-6-PE, TNFα-PE, IL-12-PE, and CXCL10-PE (BD) (M1-type proinflammatory markers), and TGFβ-PE, IL-10-PE, and CCL18-PE (BD) (M2-type anti-inflammatory markers), and for CD4^+^ and CD8^+^ T cells, we will assess IFNγ-BV650 (BD) by intracellular staining as above.

Whenever the quantity of PBMCs is sufficient, other functional in vitro tests on NK cells and monocytes will be set up. In particular, NK cells within PBMCs will be studied in a 4-h coculture degranulation flow cytofluorimetric assay using NK cells and erytroleucemic K562 cells through assessment of CD107a-PE or CD107a-FITC NK cell surface staining [35]. Moreover, CD14^+^ monocytes and CD3^−^CD56^+^ NK cells will be purified with specific mAbs linked to microbeads (Miltenyi Biotec) and a magnetic separator to obtain >90% purified cell populations.

Purified monocytes and purified NK cells will be cultured using RPMI 1640 medium with 10% FBS and supplementation with macrophage colony-stimulating factor and IL-2 (both Miltenyi Biotec), respectively. They will be stimulated with different stimuli (see above) and then checked for intracellular cytokines/chemokines of interest (see above). At the same time, monocytes and NK cells can be harvested at the end of the in vitro incubation culture. We will collect conditioned media for cytokine/chemokine detection using ELISA (IL-1β, IL-6, TNFα, IFNα, IL-10, IL-12, and CXCL10) according to the manufacturer’s protocol (R&D Systems).

The 4- to 5-day monocyte culture will be further stimulated for 24 h with LPS (Sigma Aldrich) and IFNγ (Miltenyi Biotec) (M1 stimulus) or IL-4 (Miltenyi Biotec) (M2 stimulus) to investigate macrophage polarization, with assessment of surface M1 markers (TNFα and CXCL10 [BD]) or M2 markers (IL-10 and CCL18 [BD]) to check the prevalence of macrophage polarization in different groups of COVID-19 patients.

The epidemiological analysis will be carried out by integrating both vaccination history and the daily data collected after hospital admission. Azienda a tutela della salute Insubria archives will provide missing data.

Considering the immunological profile, patients with COVID-19 will undergo routine examinations and the following: lymphocyte immunophenotyping; determination of C3 and C4 complement fraction activity; determination of serum immunoglobulin (IgG, IgM, IgA, and IgE) levels; serum protein electrophoresis; determination of serum angiotensin converting enzyme levels [36,37]; cytomegalovirus serology tests; and determination of serum IL-6 levels.

A specific data collection form will store information quickly, and then, data will be collected in a database.

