### Objectives

#### Primary Objective

The primary objective of the study is to explore phenotypes and estimate the activity degrees of monocytes, NK cells, and CD4^+^ and CD8^+^ T cells (including the CD4/CD8 T ratio) in COVID-19 patients’ peripheral blood. A dominant phenotype of these cell populations in patients affected by severe pneumonia could represent a possible therapeutic target. In fact, severe pneumonia and ARDS seems to follow excessive and disruptive inflammation sustained by monocytes in peripheral blood and macrophages in the lungs. NK cells play a pivotal role in antiviral responses and in regulating the activity of dendritic cells, monocytes, and macrophages, and this makes them extremely intriguing in this study. Simultaneously, cytokines and other soluble factors will be measured in plasma. Differences are expected among COVID-19 patients with varying disease severities and healthy people.

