### Statistical Methods for the Primary and Secondary Outcomes

Associations between different variables will be examined using Pearson correlation coefficients. Paired comparisons will be made using the Wilcoxon matched pairs test. Nonpaired comparisons will be made using the 2-tailed Mann-Whitney test. Multiple comparisons will be made using appropriate one-way analysis of variance (ANOVA). A *P* value <.05 will be considered statistically significant. All statistical analyses will be performed using R version 3.4.3 (R Project for Statistical Computing) and SPSS 21 (SPSS Inc).

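### Phenotype panels may be run on fresh or frozen PBMCs, but the named group comparisons take no account of sample state, so an uneven mix could pass for a severity difference

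*Protocol article*

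**What the plan says.** The Primary Objective section of the protocol article makes phenotype part of the primary readout: "The primary objective of the study is to explore phenotypes and estimate the activity degrees of monocytes, NK cells", and also of CD4+ and CD8+ T cells. It names the contrast of interest: "Differences are expected among COVID-19 patients with varying disease severities and healthy people".

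The section on preparation of plasma and isolation of PBMCs allows two sample states on each ex vivo phenotype panel:
- NK cells: "fresh or frozen total PBMCs per tube will be stained".
- Monocytes: "For ex vivo flow cytometry cell evaluation of monocyte phenotypes, 2.5×10^5^ fresh or frozen total PBMCs per tube will be stained".
- T cells: "the CD4/CD8 T ratio using 2×10^5^ fresh or frozen total PBMCs".

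The article does not say which samples are frozen, does not tie state to group or balance it, and does not say that state is recorded. For plasma, by contrast, the same section sets a single condition for everyone: storage at −80°C and assay once enrollment has ended.

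The statistical methods section states: "Nonpaired comparisons will be made using the 2-tailed Mann-Whitney test". Comparisons of several groups use one-way ANOVA, paired comparisons use the Wilcoxon matched pairs test, and associations use Pearson correlation. The threshold is P<.05.

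**The concern.** If freezing shifts the measured level of a marker, sample state becomes a second source of difference between tubes. A Mann-Whitney test or one-way ANOVA has group as its only factor, so it attributes to group whatever part of that difference lines up with group. A severity group with more frozen samples than another would then show a shifted marker with no immunological cause, and the study would read it as a severity pattern. Where shares are equal there is no bias, but the unmodelled shift adds variance.

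Mixing is plausible. The Results section says that the study started on April 27, 2020, and that the 120 patients and 30 controls were enrolled by December 2020. It also says that immunological analysis was still under way, with completion expected by December 2022. Masking of the data analysts does not help, because the problem lies in how the tubes were handled and not in who reads the results.

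**Working it through.** **Inputs from the article.** 30 per group (four patient groups and one control group), two-sided alpha 0.05, Mann-Whitney or one-way ANOVA, and a claimed detectable difference of 20% to 30%.

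**Inputs not in the article, so assumed.** A frozen-minus-fresh shift *s* of 0.5 to 1.0 SD (0.25 SD as a milder case), frozen shares *f1* and *f2* in the two groups, and normally distributed data.

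**1. The plan's own figure.** The 20-30% figure cannot be reproduced, because no SD, coefficient of variation (CV) or power is given. What 30 per group can detect with 80% power is

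(1.960 + 0.842) × √(2/30) = 0.72 SD, or 0.72/√0.955 = 0.74 SD for Mann-Whitney.

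Using 0.72 SD, a 20% difference needs a CV of at most about 0.28 (0.20/0.72), and a 30% difference a CV of at most about 0.41. There is little margin for an extra source of bias or variance.

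**2. Bias from an unequal mix.** Bias = (*f1* − *f2*) × *s*, in size:

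| Frozen shares | s = 0.5 SD | s = 1.0 SD |
|---|---|---|
| 40% v 60% | 0.1 SD | 0.2 SD |
| 30% v 70% | 0.2 SD | 0.4 SD |
| 20% v 80% | 0.3 SD | 0.6 SD |

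The largest, 0.6 SD, is 0.6/0.72 = 83% of the difference the study can detect with 80% power.

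**3. False-positive rate.** Simulated 30 v 30 comparisons with no true difference and shares fixed at the stated values; unadjusted Mann-Whitney, and a linear model with a state term:

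| Frozen shares | Unadjusted, s = 0.5 to 1.0 SD | Adjusted |
|---|---|---|
| 40% v 60% | about 5-7% | about 5% |
| 30% v 70% | about 10-25% | about 5% |
| 20% v 80% | about 19-55% | about 5% |

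If 40% and 60% are only expected shares and the counts vary by chance, the first row becomes 6-10%. With a shift of 0.25 SD the unadjusted rate is about 6% at 30% v 70% and about 7-8% at 20% v 80%.

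**4. Power with an equal mix.** The added variance is *f*(1 − *f*)*s*². At *f* = 0.5 this is 0.25 × 0.25 = 0.0625 for s = 0.5 and 0.25 × 1 = 0.25 for s = 1.0, so the SD rises to √1.0625 = 1.03 or √1.25 = 1.12. The effect of adjustment has to be judged within one type of test, because Mann-Whitney has slightly less power than a t test on normal data even with no shift (83% v 86% at a 0.8 SD difference). Simulated power at a true difference of 0.8 SD:

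| Shift | t test, unadjusted | Linear model with state | Gain |
|---|---|---|---|
| 0.5 SD | 84% | 85% | about 1 point |
| 1.0 SD | 80% | 86% | about 6 points |

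**The case against.** The strongest objection is that this is a condensed article. A full protocol, laboratory manual or SAP may fix the sample state or adjust for it, and the wording may mean only that the staining procedure suits either state. That part stands as a limit on what can be concluded. It does not remove the point. The article gives cell numbers, staining times, temperatures and fluorochromes, expressly allows two states on each panel, and names tests that cannot separate state from group.

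The second objection is about size. Neither the shift nor the shares are documented, and a small shift or mild imbalance does almost nothing. That is correct, and the figures are therefore illustrations.

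Several stronger readings are tempting, and the documents do not support them:
- *State is known for every tube and is being ignored.* The article does not say that state is recorded.
- *Mixing adds noise to every marker.* It does so only for markers that freezing shifts, and no shift is given for any of them.
- *The whole primary outcome is affected.* The Primary Endpoint section is worded in terms of function: impairment, innate hyperactivity and reduced T-cell activity. The stimulation, intracellular cytokine and degranulation assays are described without stating a sample state. The point covers the three phenotype panels, which are one part of the primary readout.
- *The groups did differ in frozen share.* A long enrollment period does not by itself align state with severity.
- *Vaccinee time points were measured in different states.* The article says nothing about sample state at T0, T1 or T2.

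**Conclusion.** The concern holds in conditional form. As written, the plan permits a mixed measurement condition on three panels that serve the primary objective, and its named tests cannot separate that condition from group. For a marker that freezing shifts, unequal shares bias the severity or control contrast.

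The size depends entirely on assumptions about the shift and the shares: negligible for a small shift or mild imbalance, and up to a 55% false-positive rate at a 1.0 SD shift with 20% v 80% frozen. The loss from an equal mix is minor. The article shows an exposure to bias; it does not show that any bias occurred. Because the immunological analysis was reported as unfinished, the protection can be added before the comparisons are made.

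**What to change.** - Record fresh or frozen for each tube and tabulate it by severity group and control group.
- Make sample state a stratum or factor in each between-group phenotype comparison: a van Elteren (stratified Wilcoxon) test in place of the plain Mann-Whitney, and a state term beside group in the linear model in place of one-way ANOVA.
- Where a group has almost only one state, restrict the comparison to the state the groups share, and say so.
- For the vaccinees, report state by time point, and run the paired comparison also on pairs measured in the same state. This is an analysis check. Requiring a single state across time points would be a matter of laboratory handling, and these subjects were already enrolled in January and February 2021.

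The cost is one recorded variable and a change to the analysis wording. If state turns out not to matter and is spread over the groups, adjustment costs almost nothing. If state and group are strongly aligned, the adjusted estimate will be less precise, which correctly shows how little the data can separate the two.

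### With the listed NK reagents, CD25 on NK cells cannot be read independently of the CD3-negative gate, because the two labels would normally share one detector

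*Protocol article*

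**What the plan says.** The point sits in the Methods section of the protocol article headed Preparation of Plasma and Isolation of PBMCs From Blood.

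- **CD3 label for NK cells.** The NK list opens with "CD3-BB700, CD56-APC, CD16-PE-Cy7, CD159a (NKG2A)-BV510". BB700 is the only CD3 conjugate given for NK phenotyping.
- **CD25 label for NK cells.** The same list ends with "CD25-PerCP-Cy5.5, CD69-PE, CD279 (PD1)-BUV737, TIGIT-BV786, CD96-BB515, and CD366 (TIM3)-BV421". PerCP-Cy5.5 is the only CD25 conjugate given for NK cells.
- **Instrument.** "Samples will be acquired using BD LSR Fortessa".
- **Gate.** After scatter gating, "NK cells will be divided into 2 cell subsets", and both are defined as CD3-negative. Pathophysiological Considerations also defines NK cells by the absence of CD3.
- **Where the other markers are read.** "Other marker expressions will be evaluated in both subsets of gated cells".
- **T-cell panel.** Later in the same section, the T-cell antibodies are "CD3-PerCP, CD4-APC, CD8-V450, and CD25-PE", so a PE conjugate of CD25 is already among the study's reagents.

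**The concern.** The NK gate asks for low CD3 signal, and CD25 is then to be measured on the cells that pass. If CD3 and CD25 are read in the same detector, a CD25-positive NK cell raises the signal that the gate requires to be low. Such a cell can be taken for CD3-positive and excluded. If it stays in, its signal still cannot be assigned to one marker or the other.

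The Primary Objective includes the phenotype and degree of activity of NK cells, and the Primary Endpoint expects hyperactive innate cells in severe disease. CD25 is an activation marker. Loss from the gate would lower the CD25-positive share, and the absolute loss would be larger where more NK cells are activated. The measured NK share in the same tube would fall too.

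**Working it through.** The plan gives no figure to reproduce. The check has two parts.

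**1. Do the listed reagents allow CD25 to be read on CD3-negative NK cells?**

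- The labels, the gate and the reading rule are stated in the article. What is added from outside is a general property of the dyes: BB700 and PerCP-Cy5.5 are both blue-laser dyes emitting near 695 to 700 nm. A filter-based instrument would normally collect both in one detector, and compensation cannot separate two dyes that share a detector.
- The list must cover several tubes, because four of its antibodies are on PE: NKG2C, NKGD2 (as printed), DNAM-1 and CD69 ("NKG2C-PE, NKGD2-PE, DNAM-1-PE, CD25-PerCP-Cy5.5, CD69-PE"). Those four can be put in separate tubes.
- CD3 and CD25 cannot be separated in that way. If CD3-BB700 is in the CD25 tube, CD3-negative means low signal in the channel that should show CD25. If CD3-BB700 is left out, the stated gate cannot be applied, and CD56-positive T cells can enter the NK population.
- The article's other CD3 conjugate, CD3-PerCP in the T-cell panel, does not help. PerCP is read in the same far-red region off the blue laser.

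So no tube split of the listed reagents gives an independent reading of CD25 on NK cells.

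**2. How large could the distortion be?**

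Let f be the true share of NK cells that are CD25-positive, and g the fraction of those that the CD3-negative gate excludes. Neither is in the documents; both are assumptions here. It is also assumed that the cells that remain are recognised as CD25-positive, which a shared detector would make difficult.

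- Observed CD25-positive share = f(1 − g) / (1 − fg)
- Relative loss of NK cells in that tube = fg

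| f | g = 25%: share / loss | g = 50%: share / loss | g = 100%: share / loss |
|---|---|---|---|
| 2% | 1.5% / 0.5% | 1.0% / 1% | 0% / 2% |
| 10% | 7.7% / 2.5% | 5.3% / 5% | 0% / 10% |
| 20% | 15.8% / 5% | 11.1% / 10% | 0% / 20% |

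Example: f = 10%, g = 50% gives 0.10 × 0.50 / (1 − 0.05) = 0.05 / 0.95 = 5.3%.

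Contrast between groups at g = 50%: a true 10% against 2% (5-fold, 8 points) reads as 5.3% against 1.0% (about 5-fold, 4.3 points). A true 20% against 2% (10-fold, 18 points) reads as 11.1% against 1.0% (about 11-fold, 10.1 points). Absolute shares and differences are roughly halved and the ratio survives. Only at g = 100% does the contrast disappear.

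**The case against.** The strongest reply is that the deciding fact is not in the article, which gives no spectra, lasers or filters. The reagent list is condensed and is not a tube plan, and laboratory detail of that kind commonly sits elsewhere. A shared detector would also tend to show itself at panel set-up, so the list may describe the staining incompletely and need not mean that biased data exist.

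Part of this stands. The filter set and tube layout are unknown, so the article does not show that any result is already biased. It does not remove the point: the spectral overlap is a basic property of the two named dyes, and the article itself fixes the labels, the gate and the rule that markers are read inside it. Followed as written, those do not yield an interpretable NK CD25 result.

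Three stronger readings are tempting, and the documents do not support them.

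- *All CD25-positive NK cells are lost, and a real difference reads as zero in every group.* That needs g = 100%. Dim cells may stay partly inside the gate, and the documents give neither f nor g.
- *NK activation as a whole is understated, so the primary hypothesis is compromised.* The objective and endpoint do not name CD25. CD69 is on another dye, and the article also plans NK degranulation (CD107a) and intracellular IFNγ, TNFα, CCL2 and CXCL10 after stimulation, with further functional tests where cells suffice.
- *CD25 is compromised throughout the study.* In the T-cell and Treg staining CD25 is on PE, so the conflict does not arise there.

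**Conclusion.** The point holds in a limited form. With the conjugates listed for NK phenotyping, CD25 on NK cells cannot be measured independently of CD3, however the antibodies are divided over tubes. Some CD25-positive NK cells, to an unknown extent, may be gated out, which would lower both the CD25-positive share and the NK share in that tube.

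The harm is to one of 13 listed antibodies and to one tube's NK share. CD69, CD107a, NK cytokines and T-cell CD25 are not affected. The conclusion assumes a conventional filter set that collects both dyes in one detector. The figures above illustrate direction and range only. The point should be corrected because the result would otherwise be uninterpretable and the remedy is cheap; it does not threaten the study as a whole.

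**What to change.** 1. **Samples not yet stained, or frozen PBMCs that remain.** Read NK CD25 with the CD25-PE conjugate already in the T-cell panel, in its own PE tube with CD3-BB700, CD56-APC and CD16-PE-Cy7. The section allows fresh or frozen cells, and Results says the immunological analysis is still running, so this may be feasible for part of the samples.
2. **Samples already stained with both dyes in one tube.** Do not report CD25 on NK cells. Take NK shares from tubes without CD25-PerCP-Cy5.5.
3. **Text.** State the tube layout for the NK panel and reconcile the CD3 and CD25 labels.

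No new reagent is needed. The cost is one more tube of 2.5×10^5 PBMCs per sample. The four PE antibodies already imply at least four tubes (4 × 2.5×10^5 = 1.0×10^6 cells), so a fifth brings the minimum to 1.25×10^6. That matters where cells are scarce, since the additional functional tests are run only if enough PBMCs are left. Where no cells remain, the cost is the loss of one marker.

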### Recruitment

The proposed study aims to analyze patients with confirmed SARS-CoV-2 infection by real-time reverse transcription polymerase chain reaction (RT-PCR) assays on throat swabs in order to identify differences in their immune responses. Patients will be recruited at the Emergency Department of “Ospedale di Circolo – ASST Sette Laghi,” University of Insubria in Varese, Italy.

A control group of healthy people will be required for further comparison of the findings. We will consider healthy people (both males and females; aged ≥18 years) without infection (negative for SARS-CoV-2), without symptoms of infectious diseases (neither chronic nor acute), and without chronic pathologies (N=30).

After the informed consent procedure, the sample will be divided into 4 subgroups according to the severity of clinical impairment, with at least 30 people in each subgroup. The severity of pneumonia cases will be measured with SMART-COP (systolic blood pressure, multilobar chest radiography involvement, albumin level, respiratory rate, tachycardia, confusion, oxygenation, and arterial pH) [30-32]. The following 4 categories of patients positive for SARS-CoV-2 infection will be analyzed: (1) asymptomatic patients (AS19); (2) mildly symptomatic patients with fever, tiredness, dry cough, diarrhea, etc and without full-blown pneumonia (PAU19); (3) patients with a diagnosis of pneumonia with a “low” risk score (SMART-COP) (POL19); and (4) patients with a diagnosis of pneumonia with a “moderate/high” risk score (SMART-COP) (ARD19).

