## Discussion

According to the medical hypothesis on which the protocol is based, young people could benefit from functional adaptation of innate immune cells induced through epigenetic reprogramming and, especially, pre-existing “partially specific” immunity to community viruses associated with the “bystander effect” of preceding vaccinations [6]. In this study, we will explore the main differences among patients infected by SARS-CoV-2 who experience the illness at different degrees of severity. We will recognize different populations of patients, each one with a specific immunological pattern. There could be differences in terms of cytokines, soluble factor serum levels, and immune cell activity (both of the innate compartment and the acquired one). In this way, the contribution of trained immunity and the bystander effect to protection against SARS-CoV-2 could be explained. Anamnestic data, such as preceding vaccinations and comorbidities, biochemical findings like lymphocyte immunophenotyping, and pre-existing persistent cytomegalovirus infection, allow depicting the risk profile of severe COVID-19. Proof of the roles of these immunological phenomena in the pathogenesis of COVID-19 can be the basis for the implementation of therapeutic immunomodulatory treatments. In addition, the definition of an immunological risk profile could tailor established therapies to each type of patient.

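### CMV serology is listed for COVID-19 patients only, so NKG2C (and, less surely, CD4/CD8) differences from healthy controls cannot be separated from CMV carriage with the data as planned

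*Protocol article*

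**What the plan says.** All references are to the protocol article.

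- **Who is tested for CMV.** At the end of Preparation of Plasma and Isolation of PBMCs From Blood, "patients with COVID-19 will undergo routine examinations and the following: lymphocyte immunophenotyping". The list closes with "cytomegalovirus serology tests; and determination of serum IL-6 levels". No section assigns CMV testing to the controls.
- **Who is phenotyped.** Under Sample Description and Collection for the Experimental Analysis, NK cells, monocytes and CD4/CD8 T cells are studied "in both the healthy group (tested negative for SARS-CoV-2) and sick subgroups (AS19, PAU19, POL19, and ARD19"). This research flow cytometry is separate from the patients' clinical immunophenotyping.
- **Markers.** The NK panel includes "CD159a (NKG2A)-BV510, NKG2C-PE, NKGD2-PE, DNAM-1-PE". The T-cell surface panel is "CD3-PerCP, CD4-APC, CD8-V450, and CD25-PE".
- **Controls.** Recruitment asks for adults negative for SARS-CoV-2, "without symptoms of infectious diseases (neither chronic nor acute), and without chronic pathologies (N=30"). CMV is not among the viral exclusions under Eligibility Criteria.
- **Use of the contrast.** The Primary Objective expects differences between severity levels and healthy people.
- **Stated role of CMV.** The Abstract's conclusions and the Discussion list several items, among them "pre-existing persistent cytomegalovirus infection, allow depicting the risk profile of severe COVID-19".
- **Tests.** The statistical section names Pearson correlation, Wilcoxon matched pairs, Mann-Whitney and one-way ANOVA.

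**The concern.** CMV carriage is usually silent, so a screen based on symptoms and chronic disease would not sort controls by it. The plan counts persistent CMV in the risk profile of severe disease, and so expects carriage to be associated with severity. If carriage also moves NKG2C, NKG2A or the CD4/CD8 ratio, a group with more carriers will differ on those markers even when COVID-19 does nothing to them.

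The two kinds of comparison stand differently. Among the four patient groups, serostatus is collected and can enter the analysis. Against healthy controls it is missing on one side, so no later analysis plan can adjust for it unless the controls are tested. At stake is a CMV difference being reported as a COVID-19 phenotype. The Primary Objective would treat a dominant phenotype in severe pneumonia as a possible therapeutic target.

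**Working it through.** **Inputs from the article.** Four patient groups of 30 and 30 controls (4 × 30 = 120; 120 + 30 = 150, which agrees with the text); two-sided Mann-Whitney test; significance at P < .05.

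**Inputs assumed.** The article gives neither CMV prevalence nor the size of any CMV effect on a marker. Both are varied below. SD means the marker's SD among people of the same CMV status.

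**The plan's own figure.** Sample Size claims that differences of 20% to 30% can be identified. This cannot be reproduced, because no SD, coefficient of variation or power is given. For scale, 30 vs 30 at 80% power detects (1.960 + 0.842) × √(2/30) = 0.72 SD.

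**Bias from CMV.** With no COVID-19 effect, the expected group difference is

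bias = (CMV effect) × (carriage in patients − carriage in controls).

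Example: 1.0 SD × (0.80 − 0.50) = 0.30 SD.

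**Hand check of that example.** Each group's variance is 1 + d²p(1−p): 1.25 for controls and 1.16 for patients. The standardised shift is 0.30 / √((1.25 + 1.16)/30) = 0.30 / 0.283 = 1.06. The rejection probability is about Φ(−0.90) + Φ(−3.02) ≈ 0.184 + 0.001 = 18.5% for a comparison of means. The Mann-Whitney simulation gives 17%, which is consistent.

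**Simulation.** Marker = N(0,1) + d × CMV, 30 vs 30, no COVID-19 effect, 4,000 replicates per cell (simulation error about 0.3 to 0.8 percentage points). Mann-Whitney rejection rates:

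| Carriage, controls vs patients | d = 0.5 SD | d = 1.0 SD | d = 1.5 SD |
|---|---|---|---|
| 50% vs 50% | 5% | 5% | 5% |
| 50% vs 60% | 5% | 6% | 8% |
| 50% vs 70% | 6% | 10% | 15% |
| 50% vs 80% | 8% | 17% | 30% |
| 40% vs 80% | 10% | 26% | 48% |

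Further scenarios fit the same pattern: 60% vs 70% gives 5%, 6% and 8% for 0.5, 1.0 and 1.5 SD; 70% vs 80% at 1 SD gives 5%; 60% vs 85% gives 7% at 0.5 SD and 13-14% at 1 SD; 50% vs 85% gives 22-23% at 1 SD and 38% at 1.5 SD.

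**With CMV known on both sides.** In every cell of the table, a linear model with group and CMV status rejects in 4% to 6%.

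**Stratum sizes.** If 80% to 85% of ARD19 carry CMV, 30 × 0.20 = 6 down to 30 × 0.15 = 4.5 patients are expected to be CMV-negative.

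**The case against.** The strongest case on the other side has five parts.

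- **The biological link is not in the article.** No section connects CMV to NKG2C, NKG2A, CD8 cells or the CD4/CD8 ratio. This stands: the link is an assumption, and the point is conditional on it.
- **A reader might infer that the plan treats CMV as a common cause of severity and of the immune readout.** It does not. The Abstract and Discussion describe a risk marker alongside vaccinations, comorbidities and other findings. Confounding needs only that carriage differ between groups, which is plausible on that description but not established.
- **A reader might infer that CMV status goes unused.** That is not supported. It feeds the risk profile and could enter the secondary correlations of clinical data with immune patterns. Adjustment among patients may also sit in a plan that is not shown, so its absence from a short statistical paragraph is not in itself an error. The one-sided collection is a different matter, because an analysis plan cannot supply missing serology.
- **A reader might infer that the healthy contrast can never be checked.** The storage provisions suggest otherwise: plasma is frozen, and remaining specimens may be kept for up to 15 years. The full protocol might also add control testing that the article omits.
- **NKG2C is one marker among many.** It is one of 13 antibodies in the NK panel and appears in no objective or endpoint. The primary hypothesis concerns function, hyperactivity and cytokine production, and severity-group comparisons bear most directly on a therapeutic target. This limits the reach of the point without removing it, since differences from healthy people are part of the primary objective.

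**Conclusion.** The point holds in a conditional form. As the article is written, CMV status is known for patients and unknown for controls, while CMV-relevant markers are compared across both with unadjusted tests. If CMV carriage shifts a marker and carriage differs between groups, some of an observed difference may be CMV and not COVID-19.

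The size depends entirely on assumptions outside the article. The false-positive rate is about 5%, so essentially no inflation, when carriage is equal or near-equal or the CMV effect is small. It reaches 38-48% only with a carriage gap of 35-40 points and a 1.5 SD effect. Quoting only the upper scenarios would overstate the problem.

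The concern is strongest for NKG2C. It is weaker for CD4/CD8, where the surface panel is narrow. Among patient groups it can be handled with data already planned; against healthy controls it needs additional testing or restraint in interpretation.

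**What to change.** 1. **Among patient groups:** compare NKG2C and NKG2A with adjustment for, or stratification by, the CMV serostatus already collected. Do the same for CD4/CD8 as a sensitivity analysis. This costs only analysis wording.
2. **Against healthy controls:** run CMV IgG on control plasma where stored material remains, and adjust in the same way. The cost is about 30 assays. The article describes storage mainly for patients, so first confirm that control plasma was kept and that consent covers the test.
3. **If controls cannot be tested:** state that NKG2C and CD4/CD8 differences from healthy controls will not be attributed to COVID-19, and limit conclusions on these markers to comparisons among patients.

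The main downside is small CMV-negative strata, perhaps 5 or 6 people in ARD19 under the higher carriage assumptions. An adjusted model is therefore preferable to stratification. The article reports enrolment complete and immunological analysis ongoing, so the change does not affect recruitment and should be written down before these comparisons are made.
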